Ventilation and air cleaning are widely recognized and well-established strategies for effectively reducing indoor air pollutants when controlling or eliminating the source of the pollutants is impractical as a remedial measure [17]. Balanced ventilation systems, often integrated with energy recovery ventilators (ERVs), simultaneously introduce filtered outdoor air and exhaust stale indoor air, diluting both particulate and gaseous pollutants while maintaining neutral air pressure within the building for optimal air exchange. ERVs can be equipped with Minimum Efficiency Reporting Value (MERV) 8 or higher filters to remove particles, allergens, and other contaminants from incoming outdoor air. Air cleaners, also known as stand-alone air filtration systems, primarily remove airborne pollutants from indoor air. High-efficiency particulate air (HEPA) filtration can remove at least 99.97% of particles with diameters of 0.3 µm, while gas-phase filtration (e.g., activated carbon filters) can adsorb some gaseous pollutants, including VOCs and odors.

Substantial empirical evidence supports the effectiveness of mechanical ventilation systems in improving indoor air quality (IAQ) in homes [18–25]. Although several clinical studies have further investigated the effects of residential ventilation systems on asthma-related health outcomes [26–31], none of these studies comprehensively assessed IAQ, including particulate and gaseous pollutants, mold, as well as temperature and humidity, and only one trial implemented a true placebo control; the others either provided no intervention to controls or had no control group. Similarly, a growing body of literature has shown that residential HEPA air cleaners can lower indoor PM and allergens and yield at least modest health benefits for a variety of populations, including individuals with asthma [17,32,33]. However, important knowledge gaps remain, including small sample sizes, short-term intervention periods, and variability in outcome measures.

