### Objectives and hypotheses

The primary objective of this study is to evaluate the comparative long-term (one-year) effects of ERVs and portable HEPA air cleaners on reducing exposure to indoor particulate and gaseous pollutants and mold, as well as on improving asthma-related health outcomes in inner-city children and adults with asthma in the Dallas-Fort Worth (DFW) area of Texas. We hypothesize that year-long use of ERVs and portable HEPA air cleaners will lead to improvements in IAQ and asthma-related health outcomes during the post-intervention period compared to the pre-intervention period, whereas control groups are expected to show no significant changes. Further, we hypothesize that two interventions will differ in both the profiles and magnitudes of IAQ and health improvements, as ERVs are designed to reduce both particulate and gaseous pollutants and help control indoor humidity to lower the risk of mold growth, whereas HEPA air cleaners primarily remove airborne particles from indoor air.

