For the 40 homes assigned to the ERV intervention, we will install a Broan-NuTone B160E75RS/T units. The required airflow rate of each unit will be determined based on the floor area and number of bedrooms, in accordance with ASHRAE Standard 62.2–2025, *Ventilation and Acceptable Indoor Air Quality in Residential Buildings* [36]. The building envelope leakage measured during the initial home assessments will be applied as infiltration credits in the ventilation rate calculations to account for natural air leakage. The ERV units will then operate continuously at the specified ventilation rate throughout the intervention period.

Sham ERVs will be installed in the same manner as active units but will be programmed to operate in recirculation mode, without supplying outdoor air or altering ventilation rates. They will draw indoor air from the home and return it without any dilution or exchange with outdoor air, as the outdoor air intake damper remains closed. Participants will not have access to the control panel settings during the study period. This modification will maintain participant blinding, as occupants will experience airflows and fan noise similar to those of active ERVs.

Forty (40) homes in the air cleaner group will receive a Medify Air MA-112 unit, primarily placed in the living room (or in the bedroom if occupants spend the majority of their time). In cases where additional eligible family members reside in the same household, an additional Medify Air MA-50 unit will be deployed in their bedrooms. Both air cleaners are equipped with HEPA and activated carbon filters. In homes assigned to the sham control group, filters will be removed from the air cleaner units. Both active and sham air cleaner units will be sealed and have identical external appearance and installation configurations to maintain participant blinding.

During scheduled home visits in the post-intervention period, field staff will check the ERV and air cleaner units to verify proper operation and confirm that blinding measures are maintained, including ensuring that ERV control panel settings remain unchanged and inaccessible to participants and that air cleaner unit seals remain intact.

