The primary analyses will follow the intention-to-treat (ITT) principle, including all randomized households analyzed according to their assigned intervention group, to evaluate the effects of ERVs and portable HEPA air cleaners on IAQ, mold reduction, and asthma-related health outcomes by comparing the intervention and control (sham) groups using repeated measures analysis of variance (ANOVA) with a within-between interaction. Pairwise comparisons will be conducted between each intervention and control group (Group 1 vs. Group 2, Group 3 vs. Group 4) and between intervention groups (Group 1 vs. Group 3), using Tukey’s Honest Significant Difference (HSD) test to adjust for multiple comparisons. Repeated monthly ACT scores will be analyzed using multivariate mixed-effects models to account for within-subject correlations over time. Per-protocol (PP) analyses will be conducted as sensitivity analyses and will include only households that adequately adhered to the assigned intervention protocol. Intervention adherence will be assessed using plug load logger data for both ERV and air cleaner units, including device operation status and operating duration [52]. Additionally, subgroup analyses will be conducted to explore whether intervention effects differ by demographic and socioeconomic characteristics, baseline asthma severity, and baseline IAQ.

For secondary analyses, multivariate linear and logistic regression models will examine associations among housing characteristics, occupant behaviors, indoor environmental exposures (e.g., air pollutants and mold), and asthma-related health outcomes. Housing characteristics will be considered as potential covariates or confounders, when applicable, based on biological plausibility and statistical considerations. Prior to multivariable modeling, correlations among environmental exposure variables (e.g., PM, NO_2_, VOCs, and mold indices) will be evaluated using Pearson or Spearman correlation coefficients, depending on data distribution. Variance inflation factors (VIFs) will also be calculated to assess multicollinearity among predictors. Highly correlated exposures will not be included simultaneously in the same model to minimize multicollinearity, overfitting, and unstable estimates.

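### Filters are removed from the sham air cleaners but not, as written, from the sham ERVs; if recirculated air passes a filter, the ERV placebo is not inert for particles

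*Protocol article*

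**What the plan says.** All statements are in the protocol article.

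- **Sham ERV (Interventions).** "Sham ERVs will be installed in the same manner as active units but will be programmed to operate in recirculation mode". On the air path: "They will draw indoor air from the home and return it without any dilution or exchange with outdoor air". The outdoor air damper stays closed. Blinding rests on the expectation that "occupants will experience airflows and fan noise similar to those of active ERVs". No other change to the sham ERV is described. ERV units run continuously through the intervention period.
- **Sham air cleaner (Interventions).** "In homes assigned to the sham control group, filters will be removed from the air cleaner units".
- **ERV filters in general (Introduction).** "ERVs can be equipped with Minimum Efficiency Reporting Value (MERV) 8 or higher filters to remove particles, allergens, and other contaminants from incoming outdoor air".
- **Expectation for the sham arms (Objectives and hypotheses).** The active devices should improve air quality and health, "whereas control groups are expected to show no significant changes".
- **Contrasts (Data management and statistical analysis plan).** "Pairwise comparisons will be conducted between each intervention and control group (Group 1 vs. Group 2, Group 3 vs. Group 4"), plus Group 1 against Group 3.

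**The concern.** The authors treat filtration as an active ingredient of the air cleaner and take it out of that sham. For the sham ERV they take out only the exchange with outdoor air. If the unit has a particle filter in the path that the recirculated air follows, then a sham unit installed as written runs for a year as a low-grade air cleaner. Particles and airborne spores are outcomes of the trial.

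Group 1 against Group 2 is the only placebo-controlled test of the ERV. A filtering sham would understate the ERV's effect on indoor-source particles and on any asthma outcome that depends on them, and it would conflict with the expectation of no change in controls. The planned safeguards would not detect the cause: the device checks cover operation, ERV control settings and air cleaner seals, and the plug load loggers record operating status and duration. None of these covers a filter inside a sham ERV.

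**Working it through.** No figure in the plan is in dispute. For context, the Table 1 entry for 24 measurements at f = 0.10 (power 0.82 at a total of 76) reproduces as 0.815, assuming a within-subject correlation of 0.5 and sphericity.

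**1. What the text fixes.** Sham and active ERVs share installation and approximate airflow. They differ in mode and damper position. Filter removal is stated for the air cleaners only. Whether the study ERV has a filter, and whether recirculated air crosses it, is not stated.

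**2. Effect of a filter, if present, on indoor-source particles.** Take a single well-mixed zone at steady state, with k the background loss rate, q the unit's airflow over home volume, and e the single-pass particle efficiency in the sham. The concentration is proportional to 1/(total loss rate).

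- Active against no device: q/(k + q)
- Sham against no device: eq/(k + eq)
- Active against sham: 1 − (k + eq)/(k + q) = (1 − e) × q/(k + q)

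The active-versus-sham relative reduction is therefore the undiluted reduction times (1 − e), whatever the home volume, airflow or background loss.

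Inputs, all assumed: 12,000 ft³ home; 75 cfm, so q = 75 × 60/12,000 = 0.375/h; infiltration 0.3/h and deposition 0.4/h, so k = 0.7/h.

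| Sham efficiency e | Sham alone | Active against sham |
|---|---|---|
| 0 (no filter) | 0% | 0.375/1.075 = 35% |
| 20% | 0.075/0.775 = 10% | 0.300/1.075 = 28% |
| 50% | 0.1875/0.8875 = 21% | 0.1875/1.075 = 17% |

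**3. Absolute scale, other assumed inputs.** With a 340 m³ home, k = 0.35 + 0.20 = 0.55/h and 50 to 100 cfm (q = 0.25 to 0.50/h), the share of the absolute contrast that is kept is k(1 − e)/(k + eq).

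- e = 10%: 83% to 86%
- e = 20%: 0.44/0.65 to 0.44/0.60 = 68% to 73%
- e = 50%: 0.275/0.80 to 0.275/0.675 = 34% to 41%

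**4. What dilution does to power.** The article gives 40 homes to the ERV arms; 20 against 20 assumes an equal split. Under a normal approximation, two-sided 0.05, without the Tukey adjustment, 80% power needs a difference of (1.960 + 0.842) × √(2/20) = 0.886 SD. If that outcome difference is diluted:

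| Dilution | Power at 20 per arm | Homes per arm for 80% |
|---|---|---|
| 10% | 71% | 25 |
| 20% | 61% | 32 |
| 30% | 50% | 41 |
| 50% | 29% | 80 |

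These rows describe dilution of whatever outcome is tested. The documents do not say how much of an asthma score difference would follow from a given particle difference.

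**5. Outdoor-origin particles.** Use the inputs of step 2, full penetration of infiltrating particles, and the same efficiency e for the active unit's supply air. Indoor/outdoor ratios are:

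- Active: (0.3 + 0.375(1 − e))/1.075
- Sham without filter: 0.3/0.7 = 0.43
- Sham with filter: 0.3/(0.7 + 0.375e)

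At e = 50% these are 0.45, 0.43 and 0.34. The active unit is already slightly above an unfiltered sham, and the sham's filter widens the gap. At e = 85% they are 0.33, 0.43 and 0.29, so the filter alone changes the sign.

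**The case against.** The strongest objection is that the key premise is not in the article. The Introduction says only that ERVs can be fitted with filters, as general background and for the incoming outdoor stream, which is the stream that the sham shuts off. Where a filter sits in the study unit cannot be read from the documents. This stands, and it is why the point is conditional. It does not dispose of the point: followed as written, the plan leaves in place any filter that is there, and it treats the two shams differently.

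A second objection is that filter fitting is a detail for a fuller protocol. That has some force, but the article does describe how each sham is made, and it names filter removal for one and only recirculation for the other.

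A third is that a sham matched on everything except outdoor-air exchange is a legitimate control that isolates ventilation. It would be, if that were the stated aim. On the article's own description, though, an ERV filter cleans outdoor air coming in. In a recirculating sham the same filter would clean indoor air, so it would add a function rather than match one.

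A fourth is that indoor particles are monitored before and after the intervention, so a fall in Group 2 would be visible. That would show a problem but would not restore an inert control.

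A reader might also infer more than the documents support:

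- **That the sham ERV is known to filter.** No statement about the study unit says so.
- **That the contrast nearly vanishes or reverses.** At 85% efficiency the 35% would fall to 5% and the outdoor-particle contrast would change sign, but nothing in the article supports that efficiency.
- **That the ERV would look worse than the air cleaner because of its control.** The planned comparison of the two devices is Group 1 against Group 3, which uses no sham.
- **That the whole ERV contrast is compromised.** A particle filter would not offset the active unit's dilution of gases, and reducing gases and controlling humidity are what the article says distinguish ERVs.

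**Conclusion.** The point holds as a conditional weakness in how the sham ERV is specified. If recirculated air passes a particle filter, Group 2 is not an inert control for particles and airborne spores. Group 1 against Group 2 is then biased for those outcomes and for any asthma effect that runs through them: toward no difference for indoor-source particles, and against the active unit for outdoor-origin particles.

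For indoor-source particles with equal airflow in the two arms, the relative reduction shrinks by the filter's efficiency: from 35% to 28% at 20%, and to 17% at 50%. The scaling follows from the model. The 35% and the efficiencies are assumptions, and no size can be given for asthma control or for the surface and dust mold measures. Gas contrasts are largely unaffected, and Group 3 against Group 4 and Group 1 against Group 3 do not involve the sham ERV.

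This is a cheap improvement, not a demonstrated flaw in the result.

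**What to change.** 1. Before any unit is installed, confirm whether recirculated air in the sham ERV passes a particle filter.
2. If it does, add a sentence to Interventions saying that this filter is removed from sham ERVs, with the housing closed so that participants cannot see it, as is already done for the sham air cleaners. If it does not, say so; the expectation of no change in controls then needs no qualification on this account.
3. Add filter status to the device checks already planned for the post-intervention visits.

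The cost is one check, one sentence, one commissioning step and one line on the visit checklist. The downside is small: without a filter, the sham's airflow or noise may need trimming to stay like the active unit's, and the unit may collect more dust over the year. The article reports that data collection has not begun, so the change costs little now; after a year of exposure no analysis could recover an inert control.

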### Environmental exposure assessments

The study will involve the measurements of indoor criteria air pollutants, mold, and environmental conditions, including temperature and relative humidity (T/RH) to assess the magnitude of exposures in homes. Research-grade air quality sensors will be deployed for approximately one week during the four scheduled visits (V1–V4). The TSI Q-Trak XP IAQ monitor (7585) and DustTrak aerosol monitor (8530) will be placed alongside the indoor low-cost sensors to provide accurate measurements of size-resolved PM, NO_2_, NO, CO, O_3_, and formaldehyde (HCHO).

Additionally, low-cost sensors will continuously collect indoor and outdoor air quality data over the two-year study period. A total of 160 sensors will be fabricated using a microcontroller (Raspberry Pi 4 Model B, 4 GB) and multiple pollutant sensors, including a Sensirion SPS30 for PM, an Adafruit SGP30 for VOCs, an Amphenol MiCS-2714 for NO_2_, and a Sensirion SCD4x for CO_2_ and T/RH, with an estimated cost of approximately $150 per unit. Those economically viable sensor selections are verified in a similar study to measure indoor environmental quality for residential buildings [37]. The low-cost air quality sensors will be deployed indoors (primarily in the living room) and outdoors (primarily in the backyard or porch area) during the first follow-up visit (V1) and will remain in place throughout the study. For each visit, the research team will log the senor readings to check the quality of data collection with proper tech maintenance on the sensors. Long-term time-series data from these sensors will be calibrated against short-term (approximately 1-week) high-accuracy measurements measured by research-grade instruments, and additional details on the calibration process are provided in the Statistical Analysis Plan section.

Moreover, the study will involve mold assessments through spore-trap analysis of air samples, direct microscopic examination of surface samples, and fungal DNA sequencing of dust samples. Indoor and outdoor air samples will be collected using an Air-O-Cell sampling cassette with a calibrated Bio-Pump (Environmental Express), surface samples with sterile cotton-tipped swabs, and dust samples from HVAC filters and/or damp areas with visible mold or water damage (e.g., kitchen and bathroom) in each home at V1 and V4. Air and surface samples will be submitted to the accredited laboratory Eurofins USA for spore-trap and direct microscopic analyses. The dust samples will be sent to Co-PI [name]’s lab for storage, DNA extraction, followed by fungal Internal Transcribed Spacer (ITS) sequencing at the North Texas Genome Center at UTA within three months of sample collection completion.

### Health outcome assessments

#### Primary outcome measures.

We will use the following measures to assess asthma control:

Asthma Control Test (ACT): Monthly ACT surveys will be administered electronically using an online survey link distributed to participants. The ACT is a 5-item, clinically validated questionnaire designed to assess the multi-dimensional nature of asthma control, including asthma symptoms, use of rescue medications, and the impact of asthma on daily functioning [38]. ACT scores range from 5 (“poor control of asthma”) to 25 (“complete control of asthma”), with a cut-off of 19 used to identify participants with suboptimal asthma control according to the Global Initiative for Asthma (GINA) guidelines: a score >19 indicates “well-controlled asthma,” whereas a score ≤19 indicates “poorly controlled asthma” [39,40]. Children under 12 years of age will complete the Childhood Asthma Control Test (C-ACT).Asthma Control Questionnaire (ACQ): In addition to monthly ACT, we will administer the ACQ during the home visits (V1-V4) to assess asthma control more comprehensively. The ACQ consists of 7 items covering asthma symptoms, rescue bronchodilator use, and lung function (FEV_1_, forced expiratory volume in one second, FEV_1_). Each scored on a 7-point scale from 0 (“no impairment”) to 6 (“maximum impairment”), and the overall score is calculated as the mean of all items, with lower scores indicating better control. Consistent with established guidelines, an ACQ score ≤0.75 will be used to identify “well-controlled asthma,” whereas a score ≥1.50 will indicate “poorly controlled asthma,” with intermediate values reflecting partially controlled asthma [41,42].

#### Secondary outcome measures.

Additionally, pulmonary function, health-related quality of life, perceived stress, and sleep quality will be assessed during each home visit (V1-V4):

Pulmonary Function Testing (PFT): PFT will be conducted by a trained research staff during the home visits (V1-V4). A portable spirometer will be used to measure forced expiratory volume in 1 second (FEV_1_), forced vital capacity (FVC), and the FEV_1_/FVC ratio, following standardized procedures. Participants will perform at least three acceptable maneuvers per visit, and the highest values will be recorded for analysis.Health-related quality of life will be assessed using the Short Form Health Survey (SF-36) for adults and the Pediatric Quality of Life Inventory (PedsQL) for children and adolescents. The SF-36 is a 36-item, validated instrument assessing eight health domains: physical functioning, role physical, bodily pain, general health, vitality, social functioning, role emotional, and mental health. Physical and Mental Component Summary scores (PCS and MCS) will be calculated as standardized T-scores (mean 50, SD 10), where higher scores indicate better overall physical or mental health [43]. The PedsQL will be administered using age-appropriate generic core versions for young children (ages 5–7), children (8–12), and adolescents (13–18). Each version consists of 23 items assessing physical, emotional, social, and school functioning. Responses are transformed to a 0–100 scale, with higher scores indicating better health-related quality of life [44].Perceived stress will be assessed using the 10-item Perceived Stress Scale (PSS) for adults and the 14-item child version (PSS‑C) for children and adolescents aged 5–18 years. Both instruments measure the degree to which individuals perceive their lives as unpredictable, uncontrollable, and overloaded. Items are rated on a 5-point Likert scale (0 = “never” to 4 = “very often”), with total scores ranging from 0–40 for the PSS and 0–56 for the PSS-C; higher scores indicate greater perceived stress [45,46].Sleep quality will be assessed using age-appropriate versions of the PROMIS Sleep Disturbance short form, which evaluates self-reported sleep quality, difficulties with initiating or maintaining sleep, restorative sleep, and overall sleep-related satisfaction over the past week. Raw scores range from 8 to 40, with higher T-scores indicating greater sleep disturbance (i.e., poorer sleep quality) [47,48].

